### Procedure

Participants will be recruited via (i) the psychological support hotlines established during the COVID-19 outbreak at the 6 hospital sites participating in the study, (ii) the psychologists and psychiatrists who consult with healthcare workers in their departments, (iii) by billposting, and (iv) by posting on the hospital websites and on targeted Facebook groups. An e-mail will be sent to department heads to inform their team members. Subjects interested in taking part in the study will be asked to consult the study website (www.masanteaussi.fr) where they will find a document with information on the aims and the scope of the study. They will then choose a time slot to be called back by an investigator who will assess the subject’s eligibility. Oral information about the study and the randomization procedure will be given to all subjects. Participants will be randomized and assigned to the intervention by the investigator. If the subject is eligible, he/she will receive an e-mail with a username and password allowing him/her to log into the platform after a 24-h period. After receiving the e-mail, participants will be able to make their first connection to the website and sign an electronic informed consent form (previously signed online by the investigator). They will then have to complete the self-report questionnaires assessing symptoms of depression, PTSD, insomnia, resilience, and rumination. Following this, they can either start their first session of the online CBT program or gain access to the bibliotherapy documents.

Their active participation in the program will last 8 weeks. Throughout the 8-week duration of the program, each participant (either in the experimental or the control condition) will have access to the psychological hotline (from Monday to Friday between 9 a.m. and 5 p.m.), if they need support in using the resources made available to them. We chose to provide supported interventions instead of fully automated, stand-alone internet-based CBT and bibliotherapy, as the latter generally have higher treatment dropout rates (74%) than those provided with therapist or administrative support (28% and 38%, respectively) [41]. Moreover, in the context of the current pandemic and its social distancing-related guidelines, actual social support has been highlighted as particularly necessary in order to improve well-being [42]. During the study, participants are allowed to benefit from any medical or psychological follow-up or to take psychotropic drugs when prescribed by a medical doctor.

Mid-therapy assessment will take place at 4 weeks after inclusion, i.e., subjects will be asked to fill out depression, PTSD, and COVID-19 infection status questionnaires in order to track potential undesirable outcomes. Eight weeks following their inclusion, participants will receive an e-mail inviting them to fill out all the self-report questionnaires. Then, an e-mail will inform them of the end of the program and of the availability of local mental health services if needed, e.g., psychologists, psychiatrists. Three and 6 months after the end of the program, participants will receive an e-mail inviting them to fill out the follow-up self-report questionnaires. At each step (4-week, 8-week, 3-, and 6-month follow-up), undesirable outcomes will be tracked: i.e., when a participant presents with significant suicidal ideation scores on the 9th item of the PHQ-9 (> 1), the investigator is automatically notified by the website and calls the participant to make the appropriate referrals (e.g., psychiatrist); if a participant is hospitalized in a psychiatric facility during the 8-week treatment phase, he or she will be removed from the study. If a questionnaire is not completed 3 days after it is due, the participant will receive a reminder via an e-mail notification. If questionnaires are not completed a week after they are due, one of the investigators will call the participant and invite him/her to complete it. At any time during the intervention period and after completing the program, subjects are free to withdraw their participation without justifying their motives. No further data will be collected for these participants.

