## Methods/design

### Design

Our project consists of a six-site, prospective, randomized, open and parallel group-controlled study with two arms: an experimental arm with 7 online CBT sessions and an active control arm consisting of online bibliotherapy. In addition to these interventions, each participant enrolled in the study will be informed that they can make use of the psychological hotline via the website throughout the 8-week treatment duration, in case they need to have access to a qualified therapist. The study was approved by the relevant local ethics committee (Comité de Protection des Personnes Ile-de-France VI, May 7, 2020, N 36-20) and registered at ClinicalTrials.gov on 24 March 2020 (study identifier NCT04362358).

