The following measures will be used to assess acceptability: the number of participants having completed the program (i.e., ≥ 5/7 sessions) compared to the number of participants connected to the platform (number of drop-outs); the program completion time (from minimum 3 weeks to maximum 8 weeks); the utility of each session, assessed via the VAS after each session; how often the telephone hotline was used; and over the course of the 7 sessions, the relative ratings of perceived stress and self-efficacy and how often subjects practiced the skills associated with each session (Table 1).

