### Randomization

Randomization will be carried out using the CLEANWEB® software. The randomization will be stratified by the investigation center with a 1:1 ratio for allocation to the 2 groups. Blocks of varying sizes will be randomly selected. The allocation sequence was configured by our data manager who is blinded to the allocation group. Participants will be informed of the group which they are allocated to.

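### The Procedure places randomisation before e-consent and before the baseline questionnaires, and nothing withholds the arm until both are complete

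*Protocol article*

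**What the plan says.** The Procedure section of the protocol article describes entry in this order:

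1. A telephone call: "They will then choose a time slot to be called back by an investigator who will assess the subject’s eligibility".
2. Oral information on the study and on how randomisation works.
3. Allocation: "Participants will be randomized and assigned to the intervention by the investigator".
4. An e-mail with log-in details, usable after 24 hours.
5. Consent: after that e-mail, "participants will be able to make their first connection to the website and sign an electronic informed consent form". The investigator has already signed the form online.
6. Baseline: "They will then have to complete the self-report questionnaires assessing symptoms of depression, PTSD, insomnia, resilience, and rumination".
7. Access to the first CBT session or to the brochures.

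The Design section calls the trial a "prospective, randomized, open and parallel group-controlled study with two arms". The Randomization section adds: "Participants will be informed of the group which they are allocated to". It does not say when.

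The Statistical analyses section treats J0 and S8 as the two outcome times for PSS-10 and tests the group-by-time interaction. It promises an intention-to-treat analysis, with multiple imputation if data are missing completely at random or at random. For acceptability, the Secondary outcomes section sets programme completers "compared to the number of participants connected to the platform (number of drop-outs").

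**The concern.** A randomised comparison is protected only if everyone allocated is followed and counted, and if baseline is measured before the arm can influence it. In the order described, a person has an arm for at least a day before agreeing to take part. Anyone who then does not log in and sign is lost after randomisation. The protocol itself expects the brochures to work less well than the CBT programme (Background; Active control condition), so unequal refusal is plausible if people know what they were given.

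Such loss reaches the primary outcome. People who never consent supply no week-8 questionnaire, and the article does not say whether they belong to the intention-to-treat set. If their absence depends on the arm and on how stressed or motivated they are, the missing-at-random condition behind the imputation may fail.

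The second risk is to baseline. The scales completed after log-in are self-reported. If the participant already knows the arm, the answers may reflect it, and a shifted baseline feeds into any analysis of change.

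**Working it through.** **Order of events.** Every act of the investigator in the Procedure section (call, oral information, allocation, own signature on the form) comes before the participant's first connection. No investigator step is described between the questionnaires and access to content. To place allocation after consent, the reader must supply a step that the text does not contain.

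**Which baselines are exposed.** The post-consent list names depression, PTSD, insomnia, resilience and rumination, but not PSS-10. An initial PSS-10 below 16 is an exclusion criterion (Study population), so a PSS-10 score is presumably taken by the time of the eligibility call. No section says that this score is J0. The Sample size section adds to the doubt: it includes a 10% allowance for initial PSS-10 below 16 within the 120, while the Abstract speaks of randomising 120 people already above the threshold.

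**The plan's own figure.** Inputs from Sample size: 19.6 against 16 at week 8, so a difference of 3.6; SD 5; 46 per group; alpha 5%, taken as two-sided. SD 5 fits a week-8 comparison, or a change score with a baseline to week-8 correlation of 0.5, which is not stated.

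- SE = 5 × √(2/46) = 1.04.
- Power = Φ(3.6/1.04 − 1.96) ≈ 93%. This agrees with the stated power of more than 90%.

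Moving consent and baseline ahead of allocation changes none of these figures.

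**Bias from selective entry (assumed inputs).** If a fraction f of one arm never enters, and their mean PSS-10 change would have differed by D points from that of those who enter, the arm mean among entrants is off by f × D.

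| f | D = 2 | D = 5 |
|---|---|---|
| 5% | 0.1 | 0.25 |
| 10% | 0.2 | 0.5 |
| 20% | 0.4 | 1.0 |

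With loss in both arms and the same D, the net bias is the difference in f times D. At 5% of 60 (3 people) against 15% of 60 (9 people), it is 0.10 × 2 = 0.2 to 0.10 × 5 = 0.5 points.

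**Effect on the primary test.** A bias b passes one for one into the group-by-time contrast. Two-sided type I error = 1 − Φ(1.96 − b/1.04) + Φ(−1.96 − b/1.04).

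| b (PSS-10 points) | Share of 3.6 | Type I error |
|---|---|---|
| 0.5 | 14% | about 8% |
| 1.0 | 28% | about 16% |
| 2.0 | 56% | about 48% |

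The same table applies to an arm-related shift in the J0 PSS-10, but only if J0 is scored after the arm is known. The article gives no planned effect for the secondary scales, so a shift there cannot be set against one.

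**Completion denominator (assumed counts).** Suppose 33 of 60 people randomised to CBT complete at least 5 sessions. Over all randomised this is 33/60 = 55%. If 6 never connect, the planned figure is 33/54 = 61%; if 12 never connect, it is 33/48 = 69%.

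**The case against.** The order is read from the position of sentences. The sentence after allocation opens with the eligibility condition ("If the subject is eligible, he/she will receive an e-mail with a username and password allowing him/her to log into the platform after a 24-h"), so a strictly literal reading would have people randomised whether eligible or not. The paragraph may therefore not be fully chronological, and the allocation sentence may only say who randomises. The flow chart and the schedule table, which might settle the order, could not be read in the text available for this review. This lowers certainty about what the sites will do. It does not remove the point: no section puts consent or baseline before randomisation, and the natural reading is the order set out above. If a figure shows otherwise, the Procedure text contradicts it and needs correcting.

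A reader might infer more than the documents support:

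- *That participants know their arm when they consent and complete baseline.* The time of disclosure is not given. Arm-specific content opens only after the questionnaires, which would fit disclosure at that point.
- *That the primary baseline is contaminated.* PSS-10 is not in the post-consent list and may be scored at the call.
- *That those who do not sign leave no data at all.* Eligibility screening implies at least a PSS-10 and a PHQ-9 item 9 score. Whether these may be used without consent is a separate question.
- *That acceptability is overstated.* The denominator is stated openly, the analysis is descriptive, and completion among connected users is a legitimate usage measure.

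These objections make the baseline risk conditional. The entry risk is less affected. The investigator who calls and allocates can know the arm before consent in any case, and nothing prevents its being passed on.

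**Conclusion.** The point holds in this form: as written, randomisation precedes e-consent and the secondary baseline questionnaires in an open trial, with no stated safeguard on when the arm is revealed. Loss between randomisation and consent is possible, may differ by arm, and bears on the primary comparison. The planned intention-to-treat analysis and imputation cannot reliably repair it. Influence of the arm on the secondary baselines is a risk only if disclosure comes before log-in; for PSS-10 it also requires that J0 be a later score than the screening one.

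The size is not known. Under the assumed losses of 5% to 20% in one arm and differences of 2 to 5 points, the bias is 0.1 to 1.0 PSS-10 points, or 3% to 28% of the planned 3.6. These inputs are illustrations, not figures from the documents, and the direction of any bias cannot be fixed in advance. The completion denominator is a minor addition. The order should be settled before enrolment opens, because analysis cannot dependably undo the problem afterwards.

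**What to change.** State in the Procedure section, and configure on the platform, this order:

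1. Eligibility call with PSS-10.
2. Log-in and e-consent.
3. All baseline questionnaires, with the J0 PSS-10 identified as a score taken before randomisation.
4. Allocation in CLEANWEB, released only when steps 2 and 3 are complete.
5. Disclosure of the arm, then the credibility and expectancy questionnaire (the only baseline measure that should follow allocation, since it rates the person's own treatment), then access to content.

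Define the intention-to-treat set as everyone randomised, and show all of them in the participant flow. As a smaller change, report programme completion over all those randomised to CBT beside the figure over those connected.

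The cost is a change of platform workflow, a short amendment, and a few more reminder calls to bring people through baseline before randomisation. Allocation is already run by software, and the Trial status section says that enrolment has not started. The sample size is unaffected.

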**Methods:**

Powered for superiority testing, this six-site open trial involves the random assignment of 120 healthcare workers with stress levels > 16 on the Perceived Stress Scale (PSS-10) to either the 7-session online CBT program or bibliotherapy. The primary outcome is the decrease of PSS-10 scores at 8 weeks. Secondary outcomes include depression, insomnia, and PTSD symptoms; self-reported resilience and rumination; and credibility and satisfaction. Assessments are scheduled at pretreatment, mid-treatment (at 4 weeks), end of active treatment (at 8 weeks), and at 3-month and 6-month follow-up.

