### Sample size

The number of subjects required was calculated based on the data from Rose et al. [25] which showed a relative decrease in the PSS-10 score of 15% in the control group and 30% in the experimental group. Mean score values with a standard deviation (< 5) were reported. Given that the healthcare professionals recruited in our study will be under greater stressors than Rose et al.’s [25] study sample, which consisted of college students, the expected values of PSS-10 at baseline are 23 ± 5 with a decrease to 19.6 ± 5 in the control group and 16 ± 5 in the experimental group. Simulations using a mixed linear regression model showed that 46 subjects per group, i.e., 92 in total, would be needed to highlight a difference between groups with a power of more than 90% and an alpha risk set at 5%. Considering an estimation of 10% of exclusions (initial PSS-10 < 16) and 20% of drop-outs, the number of subjects in the study was increased to 120 subjects in total (Fig. 1).

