### Outcomes

#### Primary outcomes

The decrease of the Perceived Stress Scale – 10 items version (PSS-10) [30] score at 8 weeks will be our primary outcome. The 10 items of the PSS range from 0 (never) to 4 (very often); higher scores are indicative of higher perceived stress. The PSS-10 is validated in French [32], and its ease of use and psychometric properties have been widely studied in professional contexts [33]. The expected PSS-10 values are 23 ± 5 initially with a decrease to 19.6 (control group) and 16 (experimental group).

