### Statistical analyses

A descriptive analysis will be performed on the entire population and in each group (experimental and control). Categorical variables will be described, giving the numbers and frequency of each modality. Quantitative variables will be described using the usual positional and dispersion parameters. The data analyst will be blinded as he will not participate to data collection.

We will carry out the statistical analysis of the main judgment criterion using a mixed model, including a “group” effect (experimental or control), a time effect (J0 and S8), an interaction between the “group” and the “time,” and a “subjects” effect and a “center” effect. The “subject” and “center” effects will be random effects. The statistical test of interest will focus on the interaction term between group and time, which will assess whether the decrease in the PSS-10 score is greater in the experimental group than in the control group. In a second step, if this test is significant, we will estimate the decrease difference between the groups.

As of the analyses of secondary endpoints, we will assess the efficacy of online CBT on the prevention of PTSD, insomnia, and depression at 3 and 6 months using mixed regression models. In the case of restricted scores with values close to the extremes, we may use beta regression models after transformation of the variable of interest on a scale of ]0;1[. Regarding the predictive factors of the efficacy of online CBT, we will also use the aforementioned models, incorporating an interaction between group, time, and each potential predictive factor to test whether the improvement of scores in the CBT group relies on another factor. Also, we will carry out the identification of potential mediating factors explaining the effect of CBT on professional stress using Bayesian networks that allow learning the structure of a system from the data while integrating hypotheses about the structure. Mediation formulae will be used to assess total, direct and indirect effects. Finally, we will perform a descriptive analysis of the indicators of acceptability and satisfaction.

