In order to minimize attrition bias, an intention to treat analysis and specific techniques for handling missing data will be performed. Missing data will be described variable by variable and as a whole in order to search for monotonous patterns. In order to determine the process of generating the missing data (MCAR: missing completely at random, MAR: missing at random or MNAR: missing not at random), dummy variables for whether a variable is missing will be created and cross-tabulated with others observed variables. Multivariate logistic regression can be used to determine a set of variables associated with the probability of observation. In the case of MCAR or MAR processes, multiple imputation methods will be used.

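### By the text, no PSS-10 is taken between baseline and week 8, so missing week-8 scores must be imputed without an on-treatment stress score common to both arms

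*Protocol article*

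**What the plan says.** The abstract lists five assessment times: "Assessments are scheduled at pretreatment, mid-treatment (at 4 weeks), end of active treatment (at 8 weeks), and at 3-month and 6-month follow-up". The Procedure section gives the content of the 4-week one: "subjects will be asked to fill out depression, PTSD, and COVID-19 infection status questionnaires", with the stated purpose of watching for unwanted effects. It then describes week 8 differently: "Eight weeks following their inclusion, participants will receive an e-mail inviting them to fill out all the self-report questionnaires".

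Under Primary outcomes, the decrease in PSS-10 "score at 8 weeks will be our primary outcome". Under Statistical analyses, the mixed model for this outcome contains "a time effect (J0 and S8", that is, baseline and week 8. Sample size allows for "20% of drop-outs".

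For missing data, the Statistical analyses section plans intention to treat, an examination of which observed variables go with missingness, and multiple imputation under MCAR or MAR. On the examination it says: "Multivariate logistic regression can be used to determine a set of variables associated with the probability of observation". It does not restrict which variables enter the imputation model.

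Stress is also rated on visual analog scales before and after each session, but the Table 1 footnotes place these session ratings in the experimental group. Participants who withdraw give no further data (Procedure).

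**The concern.** Multiple imputation under MAR is only as credible as the data observed before a participant is lost. The variable most likely to drive late drop-out in a stress-reduction trial, and to predict week-8 stress, is how stressed the person is part-way through. By the text this is not measured on the outcome scale in either arm, although everyone is already contacted online at 4 weeks. Cross-tabulating missingness against observed variables cannot reveal dependence on a score that was never collected.

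Different drop-out patterns in the two arms are plausible. The trial is open, participants know their group, and session reminders and calls for missed sessions are described only for the CBT arm. If those who leave one arm are selected on early response and those who leave the other are not, imputation leaves a bias in the week-8 difference. The analysis plan cannot repair this later, because the data would not exist.

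**Working it through.** **1. The plan's own figures.** Expected week-8 means are 19.6 (control) and 16 (CBT), SD 5, so the difference is 19.6 − 16 = 3.6. With a baseline to week-8 correlation of 0.5 (assumed; the article gives none), the SD of change is 5 × √(2 × (1 − 0.5)) = 5. At two-sided 5%, 46 per group then gives 93.2% power, which agrees with the stated figure of more than 90%. The check below therefore uses 3.6, SD 5, and 20% loss per arm.

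**2. What a week-4 PSS-10 would add.** Assumed correlations: 0.6 (baseline with week 4), 0.7 (week 4 with week 8), 0.5 (baseline with week 8).

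- Baseline alone explains 0.5² = 0.25 of the week-8 variance.
- With both scores, the regression weight of week 4 is (0.7 − 0.5 × 0.6)/(1 − 0.6²) = 0.40/0.64 = 0.625. The weight of baseline is (0.5 − 0.7 × 0.6)/0.64 = 0.08/0.64 = 0.125.
- Together they explain 0.125 × 0.5 + 0.625 × 0.7 = 0.0625 + 0.4375 = 0.50.

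Under these assumptions the explained share doubles, and most of the weight falls on the score that the text does not collect.

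**3. Bias, drop-out related to response in the CBT arm only.** Large-sample simulation (400,000 per arm), regression imputation by arm, true difference 3.6, 20% loss in each arm. CBT drop-out rises with week-4 PSS-10 at log-odds 0.1 to 0.3 per point; control drop-out is random. The proxies are two week-4 scores, each correlating 0.5 with week-4 PSS-10.

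| Imputation uses | Estimated difference | Excess over 3.6 |
|---|---|---|
| Baseline PSS-10 only | about 3.8-4.1 | 0.2-0.5 |
| Plus week-4 proxies | about 3.7-4.0 | 0.1-0.4 |
| Plus week-4 PSS-10 | about 3.6 | none |

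Relative to 3.6, the excess with proxies is 0.1/3.6 = 3% to 0.4/3.6 = 11%.

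**4. Direction.** A second run used correlations 0.5, 0.7 and 0.5 in the same order, log-odds 1 per SD (0.2 per point), 20% loss, and one proxy correlating 0.4 to 0.6 with week-4 PSS-10.

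| Who drops out | Baseline only | Plus proxy |
|---|---|---|
| Worse-off in CBT; control random | 4.0 | 3.9-4.0 |
| Worse-off in both arms alike | 3.6 | 3.6 |
| Worse-off in control; CBT random | 3.2 | 3.3 |
| Worse-off in CBT, better-off in control | 4.4 | 4.2-4.3 |

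The bias can be upward, nil or downward. In all four cases a week-4 PSS-10 in the imputation model gives 3.6, because drop-out was generated from that score.

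**The case against.** **The imputation model is not limited to baseline PSS-10.** A reader might infer that lost participants must be imputed from that single value. The article sets no such limit. Week-4 depression and PTSD scores exist in both arms, as do other baseline questionnaires and occupational data. Perceived stress at 3 and 6 months is available for those who miss only week 8, and session stress ratings exist in the CBT arm. This stands. Choosing among these variables is a matter for the analysis plan. What remains is that the proxies are weaker, removing only about a third of the bias in the illustration, and that the session ratings exist in one arm only.

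**The effect need not be overstated.** A reader might also infer an upward bias. The second table does not support that: the direction depends on who leaves each arm, and equal mechanisms give no bias. The upper end of the drop-out strength is also steep: 0.3 per point × SD 5 = 1.5 per SD, an odds ratio of about 4.5.

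**Loss may be no higher than planned.** The article estimates 20%. It also cites 28% and 38% for supported programs, but these are treatment drop-out rates. Under intention to treat, stopping the sessions is not the same as a missing week-8 questionnaire, and an e-mail reminder and a call are planned for late questionnaires. The larger rates should not be read as expected loss of the primary outcome.

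**Full recovery is built in.** The simulation makes drop-out depend on week-4 PSS-10 and lets everyone supply it. If half the drop-outs leave before week 4, the same fix gives about 3.7-3.8 at 20% loss.

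**The schedule cannot be seen.** Table 1 is not shown, and the narrative lists are not full inventories: the baseline list in Procedure also omits the PSS-10, which is certainly taken at entry. Against this, the 4-week list is introduced as a definition and contrasted with the full set at week 8.

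**Conclusion.** The point holds in limited form. By the text, no PSS-10 is collected between baseline and the primary endpoint, so MAR-based imputation for those lost between weeks 4 and 8 relies on baseline data and weaker proxies. In the CBT-only scenario at 20% loss, the error in a true difference of 3.6 is about 0.2-0.5 points from baseline PSS-10 alone and about 0.1-0.4 with proxies. It is nil if drop-out acts alike in both arms, and of opposite sign if the worse-off leave the control arm instead.

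These sizes rest on assumed correlations and drop-out strengths that the article does not give, and the premise is subject to Table 1. A two-time-point primary model is conventional and not an error in itself. The change is still worth making, because the measurement is cheap and its absence cannot be made good afterwards.

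**What to change.** 1. Check Table 1. If it schedules the PSS-10 at week 4, correct the Procedure text to match and state how the score is used.
2. If it does not, add the PSS-10 to the 4-week questionnaires in both arms.
3. Use the week-4 PSS-10, with the week-4 depression and PTSD scores, in the imputation model. Alternatively, enter it as an added time point in the mixed model with time as a category. Either way, keep the week-8 between-arm contrast as the primary test.

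The cost is ten more items at an existing online contact, a form change, and submission of the modification to the ethics committee. The article states that enrollment had not started, so every participant could be covered. The change does not help for participants lost before week 4. If the score can no longer be added, name the week-4 depression and PTSD scores as auxiliary variables and add a sensitivity analysis that lets drop-outs differ from completers by arm.
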